#### Community-oriented resource persons (CORPs)

The set of inclusion criteria to be met by any persons to be nominated by the community to participate as a CORP include the following: (i) an adult > 18 years (male or female], (ii) have completed at least primary level education with ability to read and write, (iii) may have worked as a volunteer on community project especially in the area of health and must have performed well while serving on the project, (iv) may be an unemployed healthcare worker such as trained junior community health worker (JCHEWs), or retired nurse/healthcare professional, retired civil servant with interest in providing care, (v) where married, the spouse must be supportive, (vi) must be acceptable to other members of their community, (vii) must have been resident in the community for at least one year. Two nominees will be from each community. The nominated members will participate in a 4-day training and the final selection of CORPs to participate in the study will be based on their performance at the training which will be assessed using pre- and post-training test and score at practical exercises.

### Who will take informed consent? {26a}

Informed consent will be obtained at the different level/phases of implementation. For the baseline study, informed consent will be taken from participants by the interviewing research assistants during the survey and qualitative studies. At the health facility, informed consent will be obtained from those found to be hypertensive and eligible to be recruited including consent to receive home-based follow-up care.

### Additional consent provisions for collection and use of participant data and biological specimens {26b}

This trial involves collecting biological specimens for storage. The informed consent form will have a paragraph seeking for the later use of data collected (survey data and blood samples) with assurance of confidentiality.

## Interventions

### Explanation for the choice of comparators {6b}

Comparators will be adults aged 18 years and above who are living in the control communities and receiving usual care for the management of hypertension.

### Intervention description {11a}

The highlights of the activities and assessments for intervention and control arm are shown in Table 1. The components of the intervention include the following.

**Table 1 Tab1:** Highlights of the activities and assessments for intervention and control arm

	Activity	Intervention	Control
1	Baseline survey	Yes	Yes
2	Selection, screening and standard training of CORPs on blood pressure screening	Yes	Yes
3	Training on additional information on follow-up care for hypertensive patients and CORPs coordination	Yes	No
4	Trained CORPs screen and refer community members found to have high blood pressure	Yes Referral to the designated primary healthcare centre in the community	Yes Referral will be to the community member’s health facility of choice
5	Train health facility staff in designated primary healthcare facilities on the National guideline for hypertension treatment	Yes	No
6	CORPs Monthly checking and recording of blood pressure as well as providing health education/counselling support by the CORPs	Yes	No
7	SMS messaging on medication and healthy lifestyle adherence to support follow-up care	Yes	No
8	Anthropometry measurement, e.g. weight, height and body mass index (BMI) Biochemical measurement ECG	Yes	No
9	Endline survey	Yes	Yes

#### i. Training of CORPs

A 4-day training will be conducted for selected persons to serve as CORPs using a training manual developed by the team. A pre- and post-test will be conducted to assess the knowledge gained during the training and to select those with high score and practical ability who will eventually participate in the project. At the training, draft health education materials and messages shall be revised with input by the CORPs and finalized for use (participatory approach). A refresher training will be conducted 6 weeks into the intervention and on the job refresher training shall be conducted by the supervisors as found necessary.

#### ii. Community-based education on hypertension, risk factors, complications and healthy lifestyle

The CORPs will provide health education to raise awareness on hypertension, risk factors, importance of screening, adherence to medication and healthy lifestyle practices in the community and during home visits. They will also mobilize the community to come out for screening. The pre-tested health education materials will be used to facilitate the community health education and will be distributed to the participants for their reference.

#### iii. Community-based screening, referral and linkage to health facility

The CORPs will be equipped with a tool kit consisting an OMRON digital sphygmomanometer, a weighing scale, tape rule and recording forms. They will visit homes, religious houses and organizational meetings in the community to screen for hypertension. In the intervention arm, trained CORPs will screen and refer individuals found to have high blood pressure to the primary healthcare centre in the community. Referral forms will be provided.

#### iv. Initial treatment and counselling of individuals confirmed to have hypertension in a health facility

Health workers will be provided and trained on application of the national guideline for hypertension treatment being recommended by the Federal Ministry of Health for primary health facilities across the country. At the health facility, the attending physician/health worker will confirm diagnosis of hypertension among individuals referred by the CORPs and those found to be hypertensive among persons visiting the health facility for other reasons or self-referred. The physician/health worker will commence antihypertensive medications based on the National guideline for the treatment of hypertension and provide initial counselling on medication adherence and healthy lifestyle. Thereafter, the patient will be referred back to the CORP in their community for home-based follow-up care. The patients in the intervention sites will be given 1-month clinic follow-up appointment at first visit to ascertain the follow-up process is in place, then every 2 months thereafter by the attending physician/healthcare worker. However, the physicians can use their discretions depending on the clinical status of the patient. A SMS voice messaging for treatment adherence, reminders and health messaging will be sent to participants weekly [32]

#### iv. Community-based hypertension follow-up care by CORPs

The CORPs will conduct routine follow-up patients in their homes monthly checking their blood pressure, adherence to medication and providing health education/counselling support. In addition, the CORPs will ask about their attendance to health facility as they were scheduled/advised and sought reasons for non-attendance among those who may not have adhered. The CORP will organize group lifestyle education session weekly where experiences will be shared and patients will engage in group exercises among other relevant activities. Follow-up record form will be used by CORPs to detail information on patients’ compliance with drug, the health education provided and BP measurements. A CORP will be attached to 20 hypertensive patients for follow-up care. The intervention will be for 6 months.

### Criteria for discontinuing or modifying allocated interventions {11b}

Any patient in the intervention arm who does not achieve blood pressure control over 2 follow-up visits by the CORPS or who develop complication of hypertension or found to be at risk of complication based on risk assessment may be withdrawn from the study after investigators review the case. Any CORP found not to perform effectively will be disengaged.

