### Outcomes {12}

The Primary outcomes are (i) change in baseline proportion of patients with controlled blood pressure, (ii) the mean change in blood pressure at 6 months between patients in the intervention and control communities. The secondary outcome measures are (i) change from baseline in proportion of patients adhering to medication, (ii) change in proportion of patients who are overweight/obese, smoke, take alcohol, practice unhealthy dietary habit and are physically inactive. In addition are (iii) mean improvement in quality-of-life score, (iv) percentage increase in satisfaction with care score, (v) change in awareness, knowledge, perception and practice, (vi) proportion of CORPs assessed to have good competency score, (vii) perception about quality and acceptability of home-based follow-up care delivered by CORPs, (viii) incidence of cardiovascular events among patients, (ix) change in baseline proportion of patients assessed to have high cardiovascular risk, (x) mean cost of treatment of hypertension, (xi) mean change in lipid level, urinary sodium and food sodium content. These variables will be measured at the end of the second, fourth and sixth month follow-up period.

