## Statistical methods

### Statistical methods for primary and secondary outcomes {20a}

Data analysis will be carried out using Stata MP version 14 based on the CONSORT 2010 guideline [40]. Intention-to-treat analysis will be applied. Continuous variable will be presented as mean and standard deviations (SDs) or medians with their 25th and 75th percentiles when the distribution of the data does not follow a Gaussian distribution. Categorical variables shall be presented as frequencies and percentages.

Baseline characteristics of participants in the intervention and control arms will be compared to assess balance and identify any variable that need to be adjusted in the final analysis. The primary outcome is achievement of blood pressure control at 6 months post-intervention. The effect of intervention within each of the study groups will be carried out comparing baseline and 6 months post-intervention using McNemar test. Depending on the distribution of baseline characteristics, random effect logit model will be fitted to estimate treatment effect size comparing the two groups. Similar analysis will be done for categorical secondary outcomes such as treatment adherence.

Cost-effectiveness analysis will also be carried out using the ingredient approach [41].

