### Methods in analysis to handle protocol non-adherence and any statistical methods to handle missing data {20c}

The use of CORPS who are based in the study communities and monthly home visit will help to minimize the occurrence of missing data and losses to follow-up. During analysis, sensitivity analyses will be carried out to assess the patterns of missing data and loss-to-follow-up so that appropriate decisions can be taken on whether multiple imputation methods need to be employed. The level of significance will be set at 5%.

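### Withdrawing uncontrolled patients from the study in the intervention arm only can remove likely primary-outcome failures and tilt the result towards the intervention

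*Protocol article*

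**What the plan says.** All references are to the protocol article.

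- **Withdrawal rule**, Criteria for discontinuing or modifying allocated interventions {11b}. The first group that the rule names is "Any patient in the intervention arm who does not achieve blood pressure control over 2 follow-up visits by the CORPS", and it says that such a patient "may be withdrawn from the study after investigators review the case". The same sentence covers patients in that arm who have a complication or are assessed as being at risk of one. No rule is given for control patients.
- **Trigger visits**, Community-based hypertension follow-up care by CORPs. On the visits this section says: "The CORPs will conduct routine follow-up patients in their homes monthly checking their blood pressure". Table 1 under {11a} has the row "CORPs Monthly checking and recording of blood pressure as well as providing health education/counselling support by the CORPs", marked yes for intervention and no for control.
- **Outcome**, Statistical methods {20a}: "The primary outcome is achievement of blood pressure control at 6 months post-intervention". Outcomes {12} names "change in baseline proportion of patients with controlled blood pressure" and the mean change in blood pressure at 6 months as primary. Cardiovascular events and the proportion at high cardiovascular risk are secondary.
- **Analysis set**, {20a}: "Intention-to-treat analysis will be applied".
- **Missing data**, {20c}: missing-data patterns will be examined so that "appropriate decisions can be taken on whether multiple imputation methods need to be employed".

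The article does not say whether a patient withdrawn under {11b} still has the 6-month reading taken, or how that patient is counted.

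**The concern.** The trigger is an early reading of the variable that defines the primary outcome, and it can operate in one arm only. If outcome data stop when a patient is withdrawn, the intervention arm is analysed with some of its likely failures taken out, and the control arm has no matching removal by design. Randomisation gives no protection against selection of this kind after allocation. The decision is also discretionary, and whoever reviews the case necessarily knows the arm.

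The proportion controlled and the mean change in blood pressure would both move towards the intervention. Event counts would be affected in the same direction, because complications also trigger withdrawal.

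The trigger need not be rare. Patients are enrolled because their pressure is raised or uncontrolled, and with monthly visits two can have passed by about month 2 of 6. On the plan's own assumption that 60% are controlled under the package, 40% of the intervention arm stays uncontrolled even if the package works. That is 0.40 × 300 = 120 patients, against a 10% attrition allowance of 0.10 × 300 = 30.

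**Working it through.** The plan gives no figure for the share withdrawn, so there is none to reproduce.

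**Inputs from Sample size {14}:** 30% controlled without the package, 60% with it, 10% attrition, and 600 participants, hence 300 per arm.

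**Assumption:** w, the share of uncontrolled intervention patients withdrawn and not counted, ranges from 10% to 50%.

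**Formula.** Let p be the true proportion controlled at 6 months in the intervention arm. If everyone withdrawn would have been uncontrolled at month 6, then

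observed proportion = p / [p + (1 − p)(1 − w)], and share of the arm lost = (1 − p)w.

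| True p | w | Calculation | Observed | Arm lost |
|---|---|---|---|---|
| 0.30 | 10% | 0.30/0.930 | 32.3% | 7.0% |
| 0.30 | 25% | 0.30/0.825 | 36.4% | 17.5% |
| 0.30 | 50% | 0.30/0.650 | 46.2% | 35.0% |
| 0.60 | 10% | 0.60/0.960 | 62.5% | 4.0% |
| 0.60 | 25% | 0.60/0.900 | 66.7% | 10.0% |
| 0.60 | 50% | 0.60/0.800 | 75.0% | 20.0% |

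With no true effect (30% in both arms), the spurious gain is 2.3, 6.4 or 16.2 points. In the design case the 30-point effect appears as 32.5, 36.7 or 45 points.

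**Tied to the planned attrition.** If the 10% allowance consisted entirely of uncontrolled intervention patients, 0.30/0.90 = 33.3% and 0.60/0.90 = 66.7%.

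**Why this is an upper bound.** Let a share m of the arm be withdrawn, of whom a fraction r would have been controlled by month 6. The observed proportion is then (p − mr)/(1 − m). It is largest at r = 0, which is the case tabulated. With p = 0.30 and m = 0.10:

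- r = 0 gives 0.30/0.90 = 33.3%
- r = 0.15 gives 0.285/0.90 = 31.7%
- r = 0.30 gives 0.27/0.90 = 30.0%, so no bias

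The bias favours the intervention whenever withdrawn patients are less likely than the arm as a whole to be controlled at month 6. A rule that selects on failure to reach control makes that the expected case.

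**False-positive rate.** This was simulated with 200,000 trials, 300 per arm, 30% controlled in both arms and a two-sided two-proportion z test. It ignores clustering and is not the planned random-effects model. The rate is 5.0% at w = 0, 9.1% at w = 10%, 35% at w = 25% and 95% at w = 50%. At w = 10% the arm loses 7%, which is inside the planned attrition.

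**The case against.** Several points on the other side stand.

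- **Intention-to-treat.** A reader might infer that the rule flatly contradicts it because a withdrawn patient has no 6-month reading. The article does not say so. The rule sits under a heading about the allocated intervention, an endline survey is planned in both arms, and the full protocol and analysis plan are not shown. Tension is the right word. Still, the text speaks of leaving the study, and the endline survey is described for consenting adult residents generally, with no provision for tracing withdrawn patients.
- **Size.** A reader might infer that the rule alone could produce the planned rise from 30% to 60%. The formula does give 0.30/0.475 = 63% at w = 75%, but that means losing 0.70 × 0.75 = 52.5% of the arm through a discretionary review, when 10% attrition is planned. The 46% and 75% scenarios lose 35% and 20%, also beyond the plan.
- **Interim status.** Failure to reach control over two visits is not month-6 failure, and some of those withdrawn would be controlled later.
- **Recoverability.** A reader might infer that imputation cannot help. The trigger is a blood pressure that the CORPs record, and Outcomes {12} has measurements at months 2, 4 and 6. Imputation, or a mixed model that uses those readings, could recover part of the bias. The fair criticism is that {20c} does not commit to it.
- **Control arm.** A reader might infer that it keeps all its failures. The article gives no control-arm retention figure; it shows only that this rule has no counterpart there.

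These points limit the size. They do not change the expected direction or supply the missing provision.

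**Conclusion.** The point holds as a one-sided, outcome-related route out of the study that the plan neither closes nor corrects for. The expected direction is towards the intervention.

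The size depends on a withdrawal share that the documents do not give. Within the planned 10% attrition, the inflation is at most about 3 points if nothing works (30% reads 33%) and about 7 points in the design case (60% reads 67%). Heavier use of the rule, at 25% or 50% of uncontrolled patients with no true effect, would show 36% or 46%. These figures assume that withdrawn patients drop out of the analysis and would all have been uncontrolled at month 6, so they are upper bounds for the number withdrawn. No size can be put on the mean change in blood pressure or on events, because the article gives no standard deviation or event rate.

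The finding warrants a change because even modest use distorts the test, and the text as written permits it.

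**What to change.** Reconcile {11b}, {20a} and {20c}. No clinical rule is proposed here: whether and how a patient's care changes stays with the investigators.

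1. In {11b}, separate a change of care from withdrawal from outcome assessment.
2. Take the 6-month blood pressure and complete event follow-up on every enrolled patient in both arms, unless the patient withdraws consent.
3. In {20a}, state that patients are analysed in the allocated arm whatever happened under {11b}.
4. In {20c}, replace the open decision with one prespecified missing-outcome rule applied identically to both arms. One option is multiple imputation using recorded interim blood pressure, with missing counted as not controlled as a sensitivity analysis. Counting missing as failure only for triggered intervention patients would bias the other way. Because the control arm has no CORP visits, the interim readings used should be ones taken in both arms, such as those planned for months 2 and 4.
5. Report the number withdrawn under {11b}, with reason and timing.

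The cost is a sentence in the protocol, matching consent wording, and one endline reading per affected patient. Trial status says that recruitment for the intervention had not started at the time of writing, so on that status the change can precede enrolment.

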### Strategies to improve adherence to interventions {11c}

To enhance adherence to the intervention, we have proposed the following strategies: (i) short message services on healthy lifestyle and medication adherence which will be sent to patients weekly; monthly monitoring of CORPS by supervisors, and pill counting by CORPs at home follow-up visits. There is a plan to engage drug pharmaceuticals to supply antihypertensives to patients at discounted price as much as possible.

### Relevant concomitant care permitted or prohibited during the trial {11d}

This trial involves screening, diagnosis and treatment of hypertension. The control arm will be on the standard/usual care while the intervention will have in addition to standard care follow-up care at home by trained community-oriented resource person. This is an implementation research which will be carried out in a real-life situation. There will be no concomitant care and participants will be advised to take only medications prescribed in health facilities or report any other medication that may have been taken during the period in the trial.

### Provisions for post-trial care {30}

No harm is envisaged from this trial.

### Outcomes {12}

The Primary outcomes are (i) change in baseline proportion of patients with controlled blood pressure, (ii) the mean change in blood pressure at 6 months between patients in the intervention and control communities. The secondary outcome measures are (i) change from baseline in proportion of patients adhering to medication, (ii) change in proportion of patients who are overweight/obese, smoke, take alcohol, practice unhealthy dietary habit and are physically inactive. In addition are (iii) mean improvement in quality-of-life score, (iv) percentage increase in satisfaction with care score, (v) change in awareness, knowledge, perception and practice, (vi) proportion of CORPs assessed to have good competency score, (vii) perception about quality and acceptability of home-based follow-up care delivered by CORPs, (viii) incidence of cardiovascular events among patients, (ix) change in baseline proportion of patients assessed to have high cardiovascular risk, (x) mean cost of treatment of hypertension, (xi) mean change in lipid level, urinary sodium and food sodium content. These variables will be measured at the end of the second, fourth and sixth month follow-up period.

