##### Anthropometric measurements

Anthropometric measurements will include weight, height and waist circumference taken using standard procedures. Briefly, all anthropometric measurements will be taken with the participant wearing light clothing and without shoes within the participant’s household compound. Body weight will be taken to the nearest 0.1 kg using a validated SECA digital scale placed on flat ground. Height will be taken in a standing position with heels perpendicular to the portable stadiometer, measured to the nearest 0.1 cm. BMI will be calculated as body weight divided by height squared (kg/m^2^). Overweight will be defined as BMI ≥ 25 kg/m^2^ but < 30 kg/m^2^ and obesity is defined as BMI ≥ 30 kg/m^2^ [36]. Waist circumference will be measured and recorded to the nearest 0.1 cm using a non-stretchable measuring tape at the mid-point between the lower margin of the last rib in the mid-axillary line and the iliac crest according the WHO guidelines [37]. Abdominal obesity will be defined as waist circumference ≥ 102 cm. Waist-to-hip ratio will be calculated and a value of less than 0.85 is considered as normal for women and less than 1.0 for men is normal.

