### Methods for additional analyses (e.g. subgroup analyses) {20b}

Numerical secondary outcomes such as mean change in systolic blood pressure will be analysed using two approaches. First, a difference-in-difference method [42] would be employed to compare mean SBP between baseline and 6-month post-intervention. This will be an assessment of within-group changes in blood pressure. Secondly, a linear mixed model will be implemented to determine the treatment effect as a measure of between-group comparison of intervention and control arms.

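### Weight is assessed only as the proportion overweight/obese; adding the between-arm difference in mean BMI would make a modest effect much easier to detect

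*Protocol article*

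**What the plan says.** In the protocol article, Outcomes {12}, secondary outcome (ii) is the "change in proportion of patients who are overweight/obese, smoke, take alcohol, practice unhealthy dietary habit and are physically inactive". The cut-offs are under Anthropometric measurements: "Overweight will be defined as BMI ≥ 25 kg/m^2^ but < 30 kg/m^2^ and obesity is defined as BMI ≥ 30 kg/m^2". Statistical methods {20a} gives the primary outcome a within-arm McNemar test and a random-effect logit between arms, then adds: "Similar analysis will be done for categorical secondary outcomes such as treatment adherence".

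The underlying values are to be recorded. The Anthropometric measurements section states "Body weight will be taken to the nearest 0.1 kg using a validated SECA digital scale", and height is "measured to the nearest 0.1 cm".

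Other measured quantities are treated differently. Blood pressure appears both as a proportion controlled and as a mean change. Outcome (xi) is the "mean change in lipid level, urinary sodium and food sodium content". For outcomes of that kind, section {20b} states: "Numerical secondary outcomes such as mean change in systolic blood pressure will be analysed using two approaches". The second of those approaches is a linear mixed model comparing the arms. No weight variable is listed among the numerical outcomes.

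**The concern.** Reducing hypertension risk factors is part of the stated aim, and body weight is a direct target of the intervention: the health education materials address it, and the weekly group sessions include exercise. With overweight and obese taken together, only a patient who crosses BMI 25 contributes to the outcome. Weight lost well above the cut, or below it, leaves the outcome unchanged.

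The stake is a null result caused by the scale. A real but modest effect on weight could be reported as no significant change, although the data to show it had been collected.

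**Working it through.** **The plan's own figure.** There is none for weight. The sample size section covers blood pressure control only. The protocol gives no BMI distribution, expected weight change, intracluster correlation or power for this outcome.

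**Inputs from the protocol.** 600 participants in two equal arms, 10% attrition: 600 / 2 × 0.90 = 270 evaluable per arm. Two-sided 5% (1.96). BMI cut 25.

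**Assumptions, not in the protocol.** BMI mean 26, SD 5; correlation r between baseline and 6 months 0.90-0.95; true between-arm difference 0.5 kg/m², with 0.3 and 0.8 as alternatives; no clustering at first.

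**1. Movement of the proportion.**
- Control: 1 − Φ((25 − 26)/5) = 57.9%.
- Intervention: 1 − Φ((25 − 25.5)/5) = 54.0%.
- Difference: 3.9 points.

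**2. Power on the proportion, unadjusted.** The standard error is √[(0.579×0.421 + 0.540×0.460)/270] = 0.0427. Power = Φ(0.0395/0.0427 − 1.96) = Φ(−1.04) = 15%.

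**3. Power on the proportion, adjusted for baseline status.** A logistic model in 1,500 simulated trials gives 27% (r = 0.90) and 34% (r = 0.95), with simulation error of about 1 point.

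**4. Power on baseline-adjusted mean BMI.** The standard error is 5 × √(1 − r²) × √(2/270).
- r = 0.90: 0.188, so power = Φ(0.5/0.188 − 1.96) = 76%.
- r = 0.95: 0.134, so power = Φ(0.5/0.134 − 1.96) = 96%.

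**5. Other differences, same assumptions.**

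| True difference (kg/m²) | Proportion, unadjusted | Proportion, adjusted for baseline status | Mean BMI, baseline-adjusted |
|---|---|---|---|
| 0.3 | 8% | 12-15% | 36-61% |
| 0.5 | 15% | 27-34% | 76-96% |
| 0.8 | 32% | 55-67% | 99-100% |

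**6. Clustering.** Sequence generation {16a} assigns two groups of communities in each of six LGAs, which makes 12 groups of about 540/12 = 45 evaluable patients. The design effect is 1 + 44 × ICC: 1.44 at an assumed ICC of 0.01, and 3.2 at 0.05. Dividing each z-value by the square root of the design effect (an approximation that applies the same effect to both scales) gives, at 0.5 kg/m²:
- Design effect 1.44: mean BMI 60-87%; proportion adjusted for baseline status about 20-25%.
- Design effect 3.2, r = 0.90: mean BMI about 32%; proportion about 11%.

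**7. A different set of assumptions.** Take BMI mean 24-28, SD 4.5-5.5, SD of change 1.0-1.5 and design effect 1.0-1.5. This is more favourable to both baseline-using analyses, because r = 0.90 with SD 5 implies an SD of change of 5 × √0.2 = 2.2.

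| True difference (kg/m²) | Proportion at 6 months | Change in status | Mean BMI change |
|---|---|---|---|
| 0.3 | 7-9% | 11-19% | 47-94% |
| 0.5 | 10-18% | 20-42% | 88-100% |
| 1.0 | 27-50% | 59-94% | about 100% |

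The direction is the same in every row.

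**The case against.** The other side has several fair points.

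- **The size of the weight change is assumed.** The protocol does not say how far BMI is expected to move. A reader might infer that any realistic change would almost never be detected. The figures do not support that: power on the proportion, using baseline status, is 27-34% at 0.5 kg/m² and 55-67% at 0.8, and reaches 59-94% at 1.0 under the second set of assumptions.
- **The 15% figure is not the best comparator.** The outcome is a change and the plan has a random-effect logit, so the analysis that uses baseline status is fairer. The outcomes section also mentions months 2 and 4; none of the calculations uses those values.
- **Clustering cuts both ways.** The 76-96% ignores it, and at a design effect of 3.2 mean BMI could itself miss the effect. Nor is the gain always large: at 0.3 kg/m², r = 0.90 and design effect 1.44 it is about 27% against 10%, or 17 points.
- **Collapsing at 25 is a reading.** Overweight and obesity are defined separately. If obesity is also reported, crossing 30 would count, so it is not established that weight loss in nearly all obese patients would go unseen.
- **A proportion is a legitimate outcome.** It matches the other risk-factor prevalences in the same item and the wording of the aim. The list of numerical outcomes is open-ended, so an analysis plan could add mean BMI.

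These points limit the size of the claim and argue for adding a measure over replacing one. They do not remove the point itself: the protocol chose the metric for weight, gave it only as a proportion, and treated blood pressure, lipids and sodium otherwise without giving a reason.

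**Conclusion.** The point holds as an improvement to one secondary outcome on which the trial is not sized. For a between-arm difference of about 0.3-0.5 kg/m², the stated outcome would usually miss the effect: power is at most 34% under the first set of assumptions and 42% under the second. Baseline-adjusted mean BMI is more powerful in every case examined, but it is not assured of success if clustering is strong. All power figures rest on assumed BMI values, correlations and design effects.

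A reader might take the fine recording precision, or the plan that "Waist circumference will be measured and recorded to the nearest 0.1 cm", as part of the fault. Neither is. The loss comes from the cut-off; the precision only shows that continuous values will exist, and waist is not part of the overweight/obese definition.

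One contradiction bears on either scale. Table 1 marks the anthropometry row as not done in the control arm, whereas Trial design {8} has weight and height collected in surveys of both arms. Any between-arm comparison of weight depends on which is meant.

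**What to change.** Add to secondary outcome (ii) the between-arm difference in 6-month BMI, analysed with the linear mixed model of section {20b}, with baseline BMI as covariate and clustering by community accounted for. Keep the proportion overweight/obese as the accompanying reported measure. Reconcile Table 1 with Trial design {8} on anthropometry in the control arm.

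The cost is one line of outcome wording and one more run of a model already planned. Weight and height are already described, so no new measurement is needed provided the reconciled text confirms them in both arms. The Trial status section says recruitment for the intervention has not started, so on the document's own dates the measure can still be prespecified. The downside is small: one more secondary measure to report, and a mean BMI difference is less familiar to policy readers than a proportion.
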